### ***Specific Objectives:***

1. To describe improvements in cardiovascular function at rest and on exercise among patients with a diagnosis of CHF
2. To describe the frequency of hospitalization among patients diagnosed with CHF enrolled into the cardiovascular rehabilitation program (CRP).
3. To describe the challenges that may be associated with establishment of a CRP at the QECH.

**Study design, population, sample size and sampling strategy:** This will be a prospective open label clinical trial of patients being discharged from the medical wards at QECH with a diagnosis of CHF. There will be two arms in the study with a total of 80 participants; Arm 1 will comprise of 40 patients with CHF who will receive cardiovascular rehabilitation as an intervention of interest, along with the usual cardiac medications that also include secondary prevention drugs, while 40 patients with CHF in arm 2 will be on cardiac medications that also include secondary prevention medications and education but not the exercise component of cardiac rehabilitation. Each participant will pick unlabelled sealed envelope with a paper that has a number that will determine to which group he or she will belong to. Participants will be followed up for 24 weeks. Participants in arm 1 will have regular cardiovascular exercise training once a week for 12 weeks and followed up without active exercise training for another 12 weeks. Arm 2 participants shall receive education component of cardiac rehabilitation at baseline and during the time points they will come for screening. Participants in both arms 1 and 2 will

continue to take cardiac medications as per their cardiologist's prescription throughout the study period.

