**Exclusion criteria**

- a. Failure to provide informed consent form
- b. Not willing to return for follow up visits
- c. Physical impairment that would affect participation in physical activity
- d. Coming from outside Blantyre
- e. Patients classified as high risk for cardiac events during exertion

**Data management and analysis:** Descriptive analysis will be conducted using SPSS software; frequencies and mean changes with standard deviations and confidence intervals will be used to report the effect size of the intervention. Multivariate paired T tests will be conducted to compare the changes in each variable at the five time points, and **independent t-test will be conducted to compare the changes between the two groups.** Tables and graphs will be used to present the findings.

Expected outcomes: Participants in arm 1 will have better cardiovascular function and fewer hospital admission compared with the controls during the first 12 weeks and that these benefits will remain at 24 weeks.

**Dissemination plans:** Findings from the study will be presented to QECH management and clinicians involved in managing patients with CHF. The findings will also be presented at the COMREC dissemination conference. Furthermore, the results will be submitted to a peer review journal for publication.

***Anticipated challenges:*** It is anticipated that patients may be lost to follow up and discontinue with the prescribed intervention due to transportation related costs. Therefore, the patients enrolled in this program will be assisted with the transportation costs; patients enrolled will be those who will manage to travel the distance with the allowance given. In addition, patients will be asked to come for a therapy session at the hospital once each week and do the other two sessions at home with a trained family member.

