The sample size for this study is based on detecting the effect size (the difference between the groups) of 0.6 at 80% power with a two-tailed significance level of 0.05. Using the formula above, a total sample size of 40 was obtained for each group. Owing the attrition of dropout rates of 5%, the sample size required is 80 (40 on each arm). To avoid issues of bias in participant selection, all patients will be selected from the chest clinic at the hospital. According to the chest clinic records, both sexes and different adult age groups (usually 45 years and above) are presented on each clinic day. Numbers 1 and 2 will be put on small pieces of paper, which will be placed in sealed and unmarked brown envelopes. Each participant will be asked to pick one envelop that will determine to which group she or he will belong to; this will assist in avoiding the selection bias. In addition, to ensure that the sample size is reached, discussions will be done with the head of the chest clinic to schedule more patients with CCF within the study participants' enrolment period. According to the available recommendations worldwide, 10 patients are allowed to exercise using a circuit training approach for an hour, and 3-4 therapists must be available to supervise the program to ensure safety. Because access to the Physiotherapy department at QECH to implement this pilot intervention is in the afternoon (13:00-12:00pm), and the number of patients enrolled into the active Arm is 40, the College of Medicine Physiotherapy gym will be used; and therapy session will be every Wednesday from 8:30 am to 12:30 pm. Nevertheless, the Physiotherapy department at QECH will be actively involved in the care delivery of these patients at College of Medicine Physiotherapy gym throughout the study, for capacity building and to ensure continuity of care after the implementation of this study. The participants shall be recruited over a period of two months.

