While participants in the Arm 1 of the trial receive both treatment modalities of CR (counselling/education and exercise therapy) and their cardiologists' prescribed cardiac medications, participants in the Arm 2 will receive the prescribed cardiac medications and education about their condition (nature of disease, risk factor modification, compliance to medications, nutritional needs); participants in Arm 2 (the control group) will come at baseline, and after 4, 8, 12 and 24 weeks for assessment and education. Figure 2 illustrates the circuit training program that will be followed during the therapy sessions. The exercise session will start with a warm up session and end with a cool down session; both sessions will be done in a group. The Arm 1 participants shall be asked to carry out two therapy sessions for each week at home, and attend a session each week at the hospital. This will assist in reducing the travel costs and avoid losses to follow up. Nevertheless, supervision at home is essential to ensure safety of the patients and efficacy of the treatment at home. Therefore, one guardian for each participant will be trained on how they will supervise the therapy sessions at home. A one-day training for the guardians will be given. All patients will be given the same home-therapy program; box stepping, walking and jogging for a predetermined FITT based on each participants' exertion capacity. The intervention will be delivered over a 12 weeks' period; participants will visit the hospital once a week and perform the rest of therapeutic tasks at home on two extra days per week for the 3 months. After the twelve-week period, all participants will be followed up for a period of twelve more weeks. All COVID-19 preventive measures namely; hand hygiene, social distance and surface/equipment disinfection will be observed. Therapists will use surgical masks during exercise therapy sessions, and patients will be asked to put on the masks before and after the exercise therapy session because they may not be able to breath while exerting.

**Table 1.** The reference benchmark for exercise prescription

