| ACTIVITY                                      | COMPLETION DATE   | RESPONSIBLE PERSON   | Key authority |
|------------------------------------------------------|--------------------------|-----------------------------|----------------------|
| Ethical approval                                     | September-October, 2020  | Investigators               | Investigators        |
| Site permission                                      | September-November, 2020 | Investigators               | Investigators        |
| Training and final discussions with all stakeholders | December, 2020           | Investigators               | Investigators        |
| Screening for enrollment                             | January-February, 2021   | Investigators               | Investigators        |
| Therapy implementation                               | February-March, 2021     | Investigator and therapists | Investigators        |
| Data management and analysis                         | April, 2021              | Investigators               | Investigators        |
| Report writing                                       | May-July 2021            | Investigators               | Investigators        |
| Dissemination of results                             | August-October, 2021     | Investigators               | Investigators        |

**Table 4:** Budget items for the study (1USD: 750MWK)

| ITEMS     | SPECIFICATION          | QUANTITY | COST PER ITEM                                          | TOTAL COST (MK) | TOTAL COST (\$) | JUSTIFICATION                                                                                                                                                                                     |
|-----------|------------------------|----------|--------------------------------------------------------|-----------------|-----------------|---------------------------------------------------------------------------------------------------------------------------------------------------------------------------------------------------|
| PERSONNEL | Cardiologist/Physician | 1        | MK20,000/session for 12 sessions                       | MK240,000       | \$320           | For medical enquiries, such as to do with medications. This will also be a focal person in all referrals into the study.                                                                          |

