|           | Physiotherapists       | 4        | MK20,000/individual/session for 12 sessions            | MK960,000       | \$1280          | For enrollment, screening and implementation. Two therapists will be needed to conduct assessments on all patients during the follow up period at 16 and 24 weeks after the implementation period |
|           |                        | 2        | MK20,000/individual/session for 2 extra patient visits | MK40,000        | \$53.3          |                                                                                                                                                                                                   |
|           | Statistician           | 1        | MK20,000/day for 10 days                               | MK200,000       | \$266.67        | To assist with data management                                                                                                                                                                    |

|           |                  |                                |                                  |               |              |                                                                                                      |
|-----------|------------------|--------------------------------|----------------------------------|---------------|--------------|------------------------------------------------------------------------------------------------------|
| EQUIPMENT | sphygmomanometer | 3                              | MK30,000                         | MK90,000      | \$120        | 15 boxes will be given to the patients for home exercise program and 16 will be used at the hospital |
|           | Stethoscope      | 3                              | MK45,000                         | MK135,000     | \$180        |                                                                                                      |
|           | Dumbbells        | 18 pairs                       | MK12,000 a pair                  | MK 96,000     | \$128        |                                                                                                      |
|           | Stepping boxes   | 31                             | MK 17,000 a box                  | MK 527,000    | \$702.67     |                                                                                                      |

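### Table 3 has no follow-up period and puts outcome analysis in April 2021, before any participant can reach week 24; its therapy window is also shorter than the 12-week programme

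*Protocol*

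**What the plan says.** **The calendar.** Table 3 in section 10.0 gives, under a column headed "COMPLETION DATE":

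- screening for enrolment: "January-February, 2021"
- therapy: "February-March, 2021"
- data management and analysis: April 2021
- report writing: May to July 2021
- dissemination: August to October 2021

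There is no row for follow-up.

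**The design.** Section 4.4 states: "The participants shall be recruited over a period of two months". Section 4.5 sets a 12-week intervention and then says: "After the twelve-week period, all participants will be followed up for a period of twelve more weeks". The Executive summary agrees: "Participants will be followed up for 24 weeks". Section 4.7 records all parameters, including admissions, at 4, 8, 12, 16 and 24 weeks. Section 6.0 plans paired tests of baseline against 3 and 6 months. The expected outcomes in the Executive summary are better function and fewer admissions in Arm 1 "during the first 12 weeks and that these benefits will remain at 24 weeks".

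**The concern.** Table 3 is the only place in the protocol that says when outcome data are analysed. If it is followed, the data are analysed before the final assessment is due for anyone.

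Three things are at stake:

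- The expectation that benefit lasts to week 24 has no data behind it, and neither does the 6-month paired comparison in section 6.0.
- The hospitalisation objective is answered over a shorter period than the follow-up the protocol describes.
- If therapy really ended on 31 March, any result labelled 12 weeks would reflect a shorter course than section 4.5 describes.

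**Working it through.** **Inputs.** Month ranges are read as first to last day.

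- Enrolment: 1 January to 28 February 2021 (Table 3; the two months agree with section 4.4).
- Therapy: 1 February to 31 March 2021 (Table 3).
- Analysis: 1 to 30 April 2021 (Table 3).
- Sessions: every Wednesday (section 4.4), for 12 weeks (section 4.5).
- Follow-up: 12 + 12 = 24 weeks. Sections 4.5 and 4.7 and the Executive summary agree on this total; only Table 3 does not accommodate it.

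**Step 1: length of the therapy window.** 28 + 31 = 59 days; 59 / 7 = 8.4 weeks, against 12 required. The Wednesdays are 3, 10, 17 and 24 February and 3, 10, 17, 24 and 31 March: 9 of 12. Even with a first session on 3 February, the twelfth falls 77 days later, on 21 April, inside the analysis month.

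**Step 2: dates of weeks 12 and 24.** Add 84 and 168 days to the start.

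| Start | Week 12 | Week 24 |
|---|---|---|
| 1 January 2021 (first enrolment day) | 26 March | 18 June |
| 1 February 2021 (first therapy day) | 26 April | 19 July |
| 28 February 2021 (last enrolment day) | 23 May | 15 August |

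**Step 3: can anyone have a week-24 value in April?** 30 April 2021 minus 168 days is 13 November 2020, before screening opens. So 0 of 80 participants have one. Follow-up is at most 90 / 7 = 12.9 weeks on 1 April and 119 / 7 = 17.0 weeks on 30 April.

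**Step 4: does the column heading help?** If the entries are completion dates, therapy could start before February but must still finish by 31 March, and analysis by 30 April. Starting on the first screening day, only participants who begin by 6 January complete 12 weeks by 31 March: 6 of 59 entry days, about 10% if entry is uniform (an assumption). If completion means the twelfth weekly session, 11 weeks after the first, the figure is 13 of 59, or 22%. The week-24 result in step 3 does not change.

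**Step 5: what calendar does the design need?** From first enrolment to last week-24 visit, 58 + 168 = 226 days; 226 / 7 = 32.3 weeks. From 1 April to 15 August is 136 days, about 4.5 months, which takes the last visit into the scheduled dissemination period.

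**Step 6: budget lines tied to the calendar.** Table 4 pays four physiotherapists "MK20,000/individual/session for 12 sessions": 4 x 12 x MK20,000 = MK960,000, as entered. For the week-16 and week-24 visits it lists 2 therapists and 2 visits at MK20,000 each. That product is 2 x 2 x MK20,000 = MK80,000; the entry is MK40,000.

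**The case against.** The strongest reply is that Table 3 is an administrative table that was never updated. The amendment request is dated 4 June 2021, after the scheduled analysis month, and section 7.0 still plans dissemination at a 2020 conference. The methods sections, the week-16 and week-24 columns of Appendices 4 and 11, and the budget for those visits all point to a 24-week study. If staff follow the methods and ignore the table, no data are lost. That is fair as to intent and limits the harm to the case where the calendar is followed. It does not remove the conflict: first enrolment to end of analysis spans 17.0 weeks whatever the start date, so shifting every row forward still leaves no room for 24 weeks.

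Three stronger readings are tempting, and the document does not support them.

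- A reader might infer that hardly anyone would have a week-12 value. That depends on the clock. Counting visits from enrolment and accepting data to 30 April, anyone enrolled by 5 February has one: 36 of 59 entry days, 61% under uniform entry. If the clock starts with therapy, spread uniformly over February, it is 5 of 28 days, 18%. The firm statement is about completing 12 weeks of therapy inside the stated window.
- A reader might infer that the hospitalisation objective could not be answered. Its wording sets no 24-week horizon, and admissions are also recorded at earlier visits. It would be truncated.
- A reader might infer that 12 funded session days are too few because staggered entry needs more. The protocol does not state rolling starts. Section 4.4 allows 10 patients per hour from 8:30 to 12:30, which is 40 per Wednesday and so the whole of Arm 1. Twelve session days fit a single cohort.

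**Conclusion.** The point stands as an internal contradiction. On every reading of Table 3, no participant reaches week 24 before the scheduled analysis ends; the shortfall is at least seven weeks (30 April against 18 June). Read literally, the therapy window holds 8.4 of 12 weeks and 9 of 12 hospital sessions, so nobody completes the programme within it. Followed as written, the calendar removes the 24-week result the protocol promises and shortens the period over which admissions are counted.

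The week-24 conclusion rests only on the dates in Table 3 and the 24-week follow-up; no entry pattern or effect size is assumed. The percentages for week 12 do assume uniform entry and are given to show the range. The document does not show that the trial intended to analyse without week 24. It shows that the only stated analysis date would have that effect.

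**What to change.** Amend Table 3 as follows:

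1. Reconcile the therapy row with the duration in section 4.5, so that the two state the same period.
2. Add a follow-up row that runs to the last enrolled participant's week-24 visit.
3. Place data lock and outcome analysis after that visit, about 32 to 33 weeks after first enrolment with two months of recruitment, and move report writing and dissemination accordingly.
4. Check that the session days and visit days funded in Table 4 match the reconciled calendar, and correct or explain the MK40,000 entry.

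The cost is a short amendment and a later report: on the 2021 dates, analysis would start in mid-August instead of April, about 4.5 months later. The budget may need a small adjustment. The visible gap is MK80,000 - MK40,000 = MK40,000, and there may be more if the follow-up visits cannot be held on two days. Sample size, outcomes and assessment weeks do not need to change.

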## APPENDICES

### Appendix 1: Risk stratification for cardiac events

| LOW-RISK                                                                                                                                                                                                                                                                                                                                                                                                                                                                                                                                                                                                    | MODERATE RISK                                                                                                                                                                                                                                                                                                                                                                                                | HIGH RISK                                                                                                                                                                                                                                                                                                                                                                                                                                                                                                                                                                                                                                                                                                                                                                                                                                                                                                                                                    |
|-------------------------------------------------------------------------------------------------------------------------------------------------------------------------------------------------------------------------------------------------------------------------------------------------------------------------------------------------------------------------------------------------------------------------------------------------------------------------------------------------------------------------------------------------------------------------------------------------------------|--------------------------------------------------------------------------------------------------------------------------------------------------------------------------------------------------------------------------------------------------------------------------------------------------------------------------------------------------------------------------------------------------------------|--------------------------------------------------------------------------------------------------------------------------------------------------------------------------------------------------------------------------------------------------------------------------------------------------------------------------------------------------------------------------------------------------------------------------------------------------------------------------------------------------------------------------------------------------------------------------------------------------------------------------------------------------------------------------------------------------------------------------------------------------------------------------------------------------------------------------------------------------------------------------------------------------------------------------------------------------------------|
| 
 
• Left ventricular ejection fraction > 50%
 
• No resting or exercise-induced complex dysrhythmias
 
• Uncomplicated MI, CABG, angioplasty, atherectomy, or stent:
 
• Absence of CHF or signs/symptoms indicating post-event ischemia
 
• Normal hemodynamic and ECG responses with exercise and in recovery
 
• Asymptomatic with exercise or in recovery, including absence of angina
 
• Maximal functional capacity at least 7.0 METs*
 
• Absence of clinical depression or depressive symptoms
 
 | 
 
• Patients neither meet High Risk nor Low Risk standards;
 
• Left ventricular ejection fraction = 40–50%
 
• Signs/symptoms including angina at “moderate” levels of exercise (60–75% of maximal functional capacity) or in recovery
 
• Mild to moderate silent ischemia (ST depression less than 2mm) with exercise or in recovery
 
 | 
 
• Left ventricular ejection fraction < 40%
 
• Survivor of cardiac arrest or sudden death 
 
• Complex ventricular dysrhythmias (ventricular tachycardia, frequent [> 6/min] multiform PVCs) at rest or with exercise
 
 
 
• MI or cardiac surgery complicated by cardiogenic shock, CHF, and/or signs/symptoms of post-procedure ischemia
 
• Abnormal hemodynamics with exercise, especially flat or decreasing systolic blood pressure or chronotropic incompetence with increasing workload
 
• Significant silent ischemia (ST depression 2mm or greater without symptoms) with exercise or in recovery
 
• Signs/symptoms including angina pectoris, dizziness, lightheadedness or dyspnea at low levels of exercise (< 5.0 METs) or in recovery
 
• Maximal functional capacity less than 5.0 METs*
 
 |

|  |  |                                                                                                            |
|--|--|------------------------------------------------------------------------------------------------------------|
|  |  | 

• Clinically significant depression or depressive symptoms

 |
|--|--|------------------------------------------------------------------------------------------------------------|

